### Interventions

Patients will be divided equally into theta-EA, gamma-EA, or sham-EA. All groups will receive conventional neurorehabilitation treatment. The trial’s intervention program will be added to the existing treatment plan for 30 min per day for 4 weeks (Monday to Friday). To ensure adherence to intervention, we will strengthen the communication between researchers and patients such as researchers will communicate with patients to determine the time point for daily intervention to ensure that treatment is received at a fixed time. The monitor committee will control procedures for monitoring adherence that two trial centers are required to track and record specific rehabilitation programs and accurate information such as the frequency and dose of medications.

#### Conventional therapy

All patients will receive basic treatment, including daily rehabilitation and clinical medications. Conventional rehabilitation treatments include physical therapy and occupational therapy. During the intervention, the patient cannot receive other acupuncture treatments or take cognitive drugs. Two trial centers are required to track and record specific rehabilitation programs and accurate information such as the frequency and dose of medications.

#### Verum EA stimulation (theta-EA group, gamma-EA group)

Patients will be treated by an experienced acupuncturist with at least 2 years of clinical experience in acupuncture. The acupuncture points selected for treatment are [Baihui (GV20)] and [Shenting (GV24)]. Before treatment, the skin at the acupoint will be disinfected with 75% ethanol. And then the acupuncturist will use one hand to fix the patients’ head and use the other hand to insert the needle into the acupuncture point (Hwato, disposable, 0.35 × 40 mm, the distributor is Suzhou Hwato Medical Devices, Suzhou, China). The insertion angle is about 10–20° (between the needle and the scalp), and the insertion depth of the needle is about 0.3–0.5 cun (1 cun = 3.33 cm). After insertion, the acupuncturist will gently twist the needle for 1 min. After “Deqi”(a feeling of soreness, tingling, or bloating), the electrode will be connected to the needle body. Then the acupuncturist will set the stimulation parameters: the theta-EA group’s stimulation frequency is 6 Hz; the gamma-EA group’s stimulation frequency is 40hz [19]. The EA device (Hwato, SDZ-III, Suzhou, China) is placed behind the patient to ensure that the patient does not know the specific frequency parameters of the intervention. Patients should receive an intervention last for 4 weeks (30 min a day, 5 days a week, Monday to Friday) [12]. During the intervention, patients are asked to be quiet to minimize other interference factors.

#### Sham-EA group

The acupuncture points and operation procedures of the sham stimulation group were consistent with those of the other two groups. The only difference from the other two groups is that the electrode connected to the needle body is actually in a no-current state [30]. The details are as follows: (1) in the sham-EA group, a special wire which cannot be powered was used, although its appearance is not different from other ordinary wires; (2) visually, the sham-EA group looks the same as the two observation groups; (3) the EA device is placed behind the patient to ensure that the patient does not know the specific frequency parameters of the intervention; and (4) when the patient is undergoing intervention, the researcher will accompany the patient to ensure that the patient looks forward and stays still in a quiet state.

#### Dropout criteria

Patients will be discontinuing interventions if they meet one or more following criteria: (a) mistakes/acceptances (subjects who were mistakenly included); (b) subjects have poor compliance and have not been treated as prescribed, for example, subjects who cannot cooperate with researchers or subjects who are unable to remain quiet and stay still or subjects who cannot come to treatment on time; (c) incomplete medical record data that affects the evaluation of efficacy; (d) subjects withdraw on their own; (e) subjects have adverse events (including recurrence of stroke or cerebral hemorrhage, stuck needles, bent needles, hematoma, pain, and metal allergy); (f) the subject’s disease has worsened severely, or some comorbidities, complications, and special physiological changes have occurred (which is unknown adverse events that we may encounter during the study); and (g) the researcher believes that the subject is not suitable to continue participating in this study.

### Outcomes

#### Primary outcome

##### Accuracy (d`) scores of visualizing 1-back digital tasks

The calculation of d` in 1-back will be described in detail in the statistics section. The patient will need to perform a visual 1-back digital task in 5 min. The patient will be asked to respond to stimuli (number shown on screen) as needed. In the 1-back, participants had to base their target/nontarget (i.e., match/not match) decision on the particular digital they saw within the sequence one trial before. The patient will be asked to press j on the keyboard as soon as possible if the numbers are the same while press f if not. This test includes 200 trials which include 40 target stimuli. Each stimulus will last for 600 ms, and then a blank screen of 1400 ms will be used as the stimulus interval [31]. The mission was edited and implemented by E-prime 3 and will be displayed on a 24-in. screen. The numbers are 2 cm high in white font with a black background. The distance is 0.8 m and the viewing angle is 1.001. The evaluation process is shown in Fig. 3.

**Fig. 3 Fig3:**
[figure not shown]
Illustration of 1-back task

#### Secondary outcome measures

##### Response time (RT) value of visualizing 1-back digital tasks

The response time usually represents the time for the subject to respond to the stimulus and is closely related to the patient’s attention. The way that select and analysis the RT value (RT-hit) is the most commonly method to evaluate the response.

##### The Rivermead Behavioral Memory Test (RBMT)

RBMT-II is mostly used to evaluate memory recovery in patients with brain injury. The test operation is simple, and the entire test process takes 20~30 min. Specific assessments include the followin g[32, 33]: (1) Remembering a person’s name. The detection method is to first show the subject the associated name and face (photo), and then, require the subject to say the corresponding name when showing the photo to him again (without telling the subject in advance that he needs to complete this test). (2) Remember 10 common items (requires subjects to name and learn) and 5 faces. The subjects are first shown some objects and faces, and then ask the subjects to identify the objects and faces that they saw initially after mixing these target stimuli with the same amount of interference stimuli. (3) Remember the main points of a piece of prose, test it immediately, and then test again after 20 min. (4) Find 5 designated points in the room according to the given route, start the test immediately, and then test again after 20 min (for patients with reduced mobility, use a model or a picture to test). At the same time, patients are required to leave a message (envelope) at each point. (5) Remember to ask for their personal items at the end of the test (after 20~30 min). These items were taken by the examiner from the patients at the beginning of the test. (6) Remember a special question (schedule your next appointment). At the beginning of the test, the tester told the patient a special question according to the instructions and then the subject should remember the question when the alarm sounded after 20 min. (7) Ten questions are used to detect the patient’s orientation to time, place, and person. Another question is to ask the patient the date of the day. Each test item is divided into the initial points, and the standard points are finally calculated. The score ranges from 0 to 24. A higher score means better memory function.

##### Trail Making Test (TMT)

TMT is a commonly used neuropsychological test that evaluates subjects’ visual search, scanning, processing speed, thinking flexibility, and executive functions. The trial tracking test consists of two sub-tests: TMT-A and TMT-B. Each sub-test consists of 25 circles distributed on a piece of paper [34, 35]. In the TMT-A evaluation section, the circles are numbered 1–25 and the circles are randomly distributed. Patients should draw lines to connect the numbers in ascending order. In part B, the circle contains both numbers (1–13) and letters (AL); as described in section A, the patient was asked to draw lines connecting circles in ascending order. The difference from part A is that in part B, the patient is asked to draw lines to connect numbers and letters (i.e., 1-A-2-B-3-C) alternately to complete the task. The test requires patients to connect the circles as soon as possible. The score for each section represents the time required to complete the task. The Chinese version of TMT-B uses numeric symbol encoding.

##### Loewenstein Occupational Therapy Cognitive Assessment scale (LOTCA)

This scale includes orientation, perception, visual motor organization, and thinking operation. The orientation includes time and place; perception includes objects, examination of agnosia, apraxia, etc.; visual motion organization includes two-dimensional graphics and three-dimensional building block copying, puzzles, drawing clocks, etc.; and thinking operations include category testing (that is, classification of item pictures), ordering of stories, and graphic reasoning [36]. Finally, the patient’s attention was scored according to his/her overall performance, and the score was calculated into the total score. The lower the score, the more obvious the dysfunction.

##### Modified Barthel Index (MBI)

MBI assesses the impairment of daily activities of patients with neurological disorders and takes the available external support (specific equipment, etc.) into account [37]. The scale rates motor and cognitive functions on a five-point scale (0–4; the higher the score, the less dependent).

##### EEG recording

When patients perform a 1-back task, their EEG signals are also recorded. The EEG signals were recorded with a 64-channel brain electrode (Bp) device at a sampling rate of 1000 Hz. All electrodes have sintered Ag/AgCl sensors that snap directly into the hat (total height 3.5 mm). The impedance recorded in the EEG remains below 8 kΩ. The ground electrode (GND) is located at Fz, and the reference electrode (reference) is located at Cz. A vertical eye movement (VEOG) electrode is located 2–3 cm from the left eye and serves as a reference electrode for online recording. Each patient is required to adjust the sitting position during the entire experiment to keep the whole body muscles, especially the facial muscles relaxed, and try not to move.

##### New blind index

Patient and evaluator blindness will be assessed separately with the new BI [29]. They will be asked which group they think they belong to and choose one of the following answers: verum-EA group, sham-EA group, or unknown. The new blind index is scaled to intervals of − 1 to 1. Among them, 1 means there is no blind method at all, 0 means completely blind method, and − 1 means the opposite guess, which may be related to unblinding.

### Data collection methods and management

Data will be collected on Case Report Forms (CRF), which will resemble the paper forms approved by the ethics committee. The data from primary outcome and secondary outcome will be transferred from the output files and assessment forms to the CRF. An identification code will be allocated for each patient during the enrolment phase to preserve anonymity. Only CRF will be allowed to record patient identification. Two data managers will type the CRF into the computer and check the paper and the electronic data. Except for the ethics committees during audit, all data will be confidential and made anonymous to anyone outside the study. About EEG data, we will solicit participants to consent that the data will be kept at the hospital for future studies. All the data will be available from the corresponding author for use and/or analysis. During the study, If the participants discontinue or deviate from intervention protocols, we will collect as much data as possible for further analysis. Plans that promote participant retention and complete follow-up are as follows: primarily, we will strengthen the communication between researchers and patients, in order to gain the understanding and cooperation of patients as much as possible; furthermore, we will give the patients corresponding financial compensation according to the number of times the patients participated, so as to encourage the patients to continue participating in the experiment until the end of the experiment; last but not least, patients will receive free relevant examination results including cognitive assessment, etc. The results of the experiment will be used to write an article for clinical research, and the article will be published in a relevant journal for professional medical workers and the public to review. The patients will also be informed with the phone number of the attending doctor while undergoing the experiment. It is convenient for them to get more information about the experiment from the attending physician.

### Sample size calculation

The primary endpoint was the difference of accuracy (d`) scores respectively at baseline and endpoint between the three groups (gamma-EA group, theta-EA group, and sham-EA group) in the 1-back test for patients with post-stroke. Since we did not have enough previous research as the basis for our estimated sample size, we chose the data collected in the previous pre-experiment to calculate the sample size required for this experiment. The null hypothesis is that *μ*_*i*_ = *μ*_*j*_ = *μ*_*t*_, while the alternative hypothesis is *μ*_*i*_ ≠ *μ*_*j*_ ≠ *μ*_*t*_, where *μ* is the mean difference and *i*, *j*, and *t* denote the sham-EA, gamma-EA, theta-EA group, respectively. Our pre-experimental results of 1-back accuracy (d`) scores show that after treatment, the d` values of the gamma-EA group (2.48 ± 0.32) and the theta-EA group (2.02 ± 0.53) are improved compared with the sham-EA group (1.88 ± 0.60). Using the sample size calculation formula for comparing the average of multiple independent samples in the parallel design, under the assumptions of α of 0.05 and (1-β) of 0.8, a sample size of 18 per group has been calculated. Considering a 20% dropout rate, a total of 66 patients will be enrolled in the trial (22 per group). The specific calculation formula is as follows [38]: *n* = λ/Δ

$$ \Delta =\frac{1}{\sigma^2}\sum \limits_{i=1}^K{\left({\mu}_i-\overline{\mu}\right)}^2\kern0.5em \overline{\mu}=\frac{1}{k}\sum \limits_{j=1}^k{\mu}_j $$

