#### The efficacy analysis will use an intention-to-treat analysis

The results of 1-back evaluation are based on the accuracy and response time as the observation indicators. The evaluation results of RBMT, TMT, LOTCA, and MBI are summarized according to the calculation rules of each scale. The results of each of the above assessments are expressed as mean ± SD. The statistical method uses analysis of variance (assuming a normal distribution) and using Kruskal-Wallis (non-parametric test) to test if it does not meet the normal distribution. The significance level was 95% (*p* values alpha < 0.05 on both sides). If the data is missed, the last observation carried forward method will be applied.

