### Outcome measurements selection

*N*-back task, as the primary outcome, is one of the traditionally been used paradigms to explore the neural basis of WM and executive function (EC) [53]. Neuropsychological studies show EC (including shifting, updating, and inhibition) is a core component of WM [54], unlike other simple storage tasks, such as forward digital span task [55]; *n*-back task is regarded as a typical task loading on WM updating [56]. In *n*-back task, participants need to decide whether the current stimulus is the same as the stimulus they saw *n* steps back. The larger the value of *n*, the higher the difficulty level of the test [57, 58]. In the pre-experiment, we booked 9 patients with cerebral infarction and randomly assigned them to the theta-EA group, gamma-EA group, and sham-EA group. The intervention parameters and course of treatment are consistent with this experiment. Before intervention, patients were evaluated 0-back, 1-back, and 2-back. It was found that 6 subjects had difficulty performing 2-back, so only 0-back and 1-back were evaluated after the intervention. The results showed that 0-back has the ceiling effect. Thus, we choose 1-back to assess patients’ working memory. In addition to dealing with behavioral evaluations, analysis of the EEG signals is also an important aspect. Studies have shown that the different components of ERP are closely related to the information processing process of working memory [59]. For example, N2 is related to the maintenance of information [60], and P3 is related to the updating of information and allocation of attentional resource [61]. Hence, we recorded the task status of the patient’s EEG signals to explore the impact of the intervention scheme on the electrical activity of the cerebral cortex, including relative to sham.

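### The 80% power is claimed for a change in d' but computed from after-treatment values with an unstated sigma, and 22 per group retains slightly fewer than the 18 required

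*Protocol article*

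**What the plan says.** All sizing statements are in the protocol article, section Sample size calculation, unless noted.

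- Endpoint: "The primary endpoint was the difference of accuracy (d`) scores respectively at baseline and endpoint between the three groups". The hypotheses are written in terms of μ, which the section defines as a mean difference.
- Inputs: "Our pre-experimental results of 1-back accuracy (d`) scores show that after treatment", the values are "the gamma-EA group (2.48 ± 0.32) and the theta-EA group (2.02 ± 0.53") and that these "are improved compared with the sham-EA group (1.88 ± 0.60"). No baseline values are given.
- Error rates: "under the assumptions of α of 0.05 and (1-β) of 0.8".
- Formula: n = λ/Δ, with Δ the sum of squared deviations of the group means divided by a single σ². Three SDs are listed; which one, or which average of them, serves as σ is not said.
- Result: 18 per group, then "Considering a 20% dropout rate, a total of 66 patients will be enrolled in the trial (22 per group").
- Source of the inputs (section Outcome measurements selection): "we booked 9 patients with cerebral infarction and randomly assigned them to the theta-EA group, gamma-EA group, and sham-EA group".
- Analysis: one-way ANOVA, or Kruskal-Wallis if the data are not normal, by intention to treat with last observation carried forward.

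**The concern.** A power statement holds only for the variable whose means and SD went into it. Here the endpoint and μ are a baseline-to-endpoint difference, while the numbers entered are levels after treatment. The SD of a change differs from the SD of a level by a factor that depends on the pre-post correlation, and the article gives no correlation. Without knowing σ, a reader cannot reproduce 18 except by trying candidates. In addition, the dropout allowance does not quite return the number the formula asked for.

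At stake is whether 66 patients support the 80% claim for the comparison the trial says it will make. If the claim is wrong in the unfavourable direction, a null result would be over-interpreted.

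**Working it through.** **Inputs.** Means 1.88 (sham), 2.48 (gamma), 2.02 (theta); SDs 0.60, 0.32, 0.53; alpha 0.05; power 0.80; three groups, 1:1:1; dropout 20%.

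**Step 1: reproduce 18.** Grand mean = (1.88 + 2.48 + 2.02)/3 = 2.1267. Sum of squared deviations = 0.0608 + 0.1248 + 0.0114 = 0.19707. λ for a chi-square with 2 df at alpha 0.05 and power 0.80 is 9.635.

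| σ tried | Δ = 0.19707/σ² | n = 9.635/Δ | per group |
|---|---|---|---|
| 0.60 (largest SD) | 0.5474 | 17.60 | 18 |
| 0.53 (theta SD) | 0.7016 | 13.73 | 14 |
| 0.498 (pooled SD) | 0.7954 | 12.11 | 13 |
| 0.483 (mean SD) | 0.8436 | 11.42 | 12 |

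The pooled SD is √[(0.60² + 0.32² + 0.53²)/3] = √0.24777 = 0.498. Of the candidates tried, only 0.60 gives 18. That value is inferred by back-calculation.

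**Step 2: dropout.** 18 × 1.2 = 21.6, rounded to 22, which matches the article. To retain 18 after losing 20% one divides: 18/0.8 = 22.5, so 23 per group (69 in total). With 22 enrolled, 22 × 0.8 = 17.6 remain. 22 retains 18 only up to 1 − 18/22 = 18.2% dropout.

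**Step 3: power for the after-treatment comparison.** The formula rests on the large-sample chi-square; the planned ANOVA uses the F distribution with 3n − 3 error df and noncentrality nΔ.

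| per group | formula, σ 0.60 | F test, σ 0.60 | F test, σ 0.498 |
|---|---|---|---|
| 17.6 | 80.0% | 77.4% | 91.2% |
| 18 | 80.9% | 78.4% | 91.8% |

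**Step 4: power for the endpoint as defined (change).** Assume equal baseline means, so that the group differences in change equal those after treatment, and equal SDs before and after. Then SD of change = σ√[2(1 − ρ)]. ρ is an assumption. F-test power at 18 per group:

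| ρ | σ 0.60 | σ 0.498 |
|---|---|---|
| 0.2 | 0.57 | 0.74 |
| 0.3 | 0.63 | 0.80 |
| 0.5 | 0.78 | 0.92 |
| 0.7 | 0.95 | 0.99 |

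At ρ = 0.5 the SD of change equals σ, so the result matches the after-treatment calculation. Below 0.5 the change endpoint needs more patients than were computed, and above 0.5 fewer.

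**Step 5: baseline-adjusted alternative.** With ANCOVA of post-treatment d' on baseline d', the residual variance is σ²(1 − ρ²) and one further error df is used. At 18 per group and σ 0.60, power is about 0.80 at ρ = 0.2 and 0.82 at ρ = 0.3.

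**The case against.** The tempting stronger reading is that the trial has about 77% power instead of 80%. The documents do not support it. By the article's own formula, the 17.6 patients left after dropout equal the unrounded requirement of 17.60 and give 80.0%. The 77.4% needs both the exact F distribution and the largest pilot SD; the pooled SD of the same figures gives 91%. Sigma cannot be called unstated and power be fixed at 77% in the same breath.

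The dropout slip is also minor, at one patient per group. It might be said that intention-to-treat analysis with carried-forward values removes it, because nominally all 22 per group are analysed (86.8% by the F test at σ 0.60). That stands only before dilution. The Study design section has two assessments, so the value carried forward is the baseline. If 20% per group are carried, with equal baselines and SD 0.60, group differences shrink to 80% and power at 22 per group is about 68%.

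A reader might also infer that the pilot's weakness is hidden. It is not: the pilot of 9 is reported under Outcome measurements selection, and the Limitation section names both the reliance on it and the small sample.

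The best objection to the main point is that the endpoint wording, with its word respectively, may mean a comparison of groups at each time point. After-treatment inputs would then fit. But μ would not then be a mean difference, and the analysis sections do not settle which is meant. The ambiguity itself needs resolving.

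**Conclusion.** The concern holds in a limited form. The stated 80% is not a power for the endpoint as defined, and it cannot be turned into one from the figures given. Over ρ from 0.2 to 0.7, power at 18 per group lies between 0.57 and 0.95 if σ is 0.60, and between 0.74 and 0.99 if σ is 0.498, so the error could go either way. These ranges assume equal baseline means, equal SDs before and after treatment, and the pilot effect sizes as the article gives them. The unstated σ is a separate defect: it moves the required size from 13 to 18 per group. The dropout arithmetic is wrong by 0.4 retained patients per group, which is immaterial beside the other two. No general shortfall in power has been shown.

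**What to change.** Keep 66 patients and revise the sample size paragraph and the primary analysis:

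1. State the σ actually used and where it came from.
2. Say that 22 per group retains 18 only up to about 18% dropout, and give power at 20% dropout conditionally on σ: 77% by the F test if 0.60, 91% if 0.498.
3. Make the primary analysis post-treatment d' adjusted for baseline d' (ANCOVA), and reword the endpoint and μ to match, so that the after-treatment inputs belong to the quantity tested. Baseline d' is already collected.
4. Show power over a range of ρ and σ in place of one figure.

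The cost is a change to the primary analysis model, now one-way ANOVA, and a slightly less favourable power statement. No extra patients or assessments are needed.
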